#### Strategies to promote participant retention and complete follow-up {18b}

Due to the fact that our patients are selected from the pediatric population, their parents will be asked to provide written feedback on the observed outcomes of the evaluations in their children in addition to the regular follow-up via phone or free-of-charge visits.

#### Data management {19}

In the current trial, the database will be generated from the questionnaire of clinical data and laboratory assay results in the Excel software and SPSS. As the trial researchers, selected and trained nurses and assistants will collect the data at baseline and during the follow-up and record the obtained data in the paper questionnaires, as well as the designed Excel datasheet. At the next stage, the data will be analyzed in the SPSS. To ensure security, the login passwords are allowed only for the trial researchers. The database is prepared to only accept the variables that are consistent with the previous entries, and it could also be altered in the case of randomly missing values. Twice a month, 10% of the electronic data will be randomly compared with the paper questionnaires, and discrepancies will lead to a 50% double-checking of the electronic data.

#### Confidentiality {27}

Data of the participants will be stored at the security site. The laboratory specimens, collected data, and reports will be identified by a coded ID number. Data collected during the course of the research will remain strictly confidential and only accessed by the research team. The corresponding author will also have access rights to the dataset. In addition, the anonymous data will be shared with other researchers to enable international prospective meta-analyses.

#### Plans for collection, laboratory evaluation, and storage of biological specimens for genetic or molecular analysis in this trial/future use {33}

This trial does not involve the collection of biological specimens for storage.

#### Statistical methods for primary and secondary outcomes {20a}

Data analysis will be performed in SPSS version 16, and data distribution will be evaluated using the Kolmogorov-Smirnov test. Data are expressed as frequencies for the qualitative variables, mean and standard deviation for the normally distributed continuous variables, and median and interquartile range for the other variables. In addition, intergroup differences will be evaluated using paired t-test for the normally distributed continuous variables and Wilcoxon rank-sum test for the other variables. Intragroup differences will be assessed using independent *t* test for the normally distributed continuous variables and Mann-Whitney *U* test for the other variables. The mean changes in the secondary outcomes will also be adjusted for the baseline data and disease severity using the analysis of covariance (ANCOVA). In all the statistical analyses, the *P* value of ≤ 0.05 will be considered significant.

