### Trial design {8}

This is a prospective, single center, double-blind, parallel, randomized placebo-controlled clinical trial. The study protocol was written following the standard Protocol Items Recommendation for Interventional Trials (SPIRIT) Checklist (Table 1).

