### Assignment of interventions: allocation

#### Sequence generation {16a}

The patients meeting the inclusion criteria will be enrolled in the study. Initially, stratified randomization will be used to divide the participants into two groups based on disease severity (severe/mild-to-moderate) using spirometry with 40% FEV1 cutoff range. Following that, random sampling will be applied to select the patients from each group to be administered with the nano-curcumin drop or nano-curcumin placebo drop using a random number table (Fig. 1).

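### The t-tests in {20a} are assigned the wrong way round: the between-arm comparison gets a paired t-test and the within-child comparison an independent one

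*Protocol article*

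**What the plan says.** All references are to the protocol article.

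- **Design.** Trial design {8} describes a "double-blind, parallel, randomized placebo-controlled clinical trial". Under Sequence generation {16a}, "stratified randomization will be used to divide the participants into two groups based on disease severity (severe/mild-to-moderate) using spirometry with 40% FEV1 cutoff range", and treatment is then allocated at random within those strata. No child is matched to another.
- **Primary outcomes.** Outcomes {12} defines them as changes from baseline to 3 months, to be compared.
- **Tests between arms.** Statistical methods {20a} states that "intergroup differences will be evaluated using paired t-test for the normally distributed continuous variables and Wilcoxon rank-sum test" for the remaining variables.
- **Tests within arms.** The next sentence reads "Intragroup differences will be assessed using independent *t* test" for normally distributed variables and "Mann-Whitney *U* test for the other variables".
- **Adjusted models.** {20a} plans an ANCOVA on baseline and disease severity, but names it only for the secondary outcomes. Additional analyses {20b} mentions ANCOVA or binary logistic regression without naming an outcome.

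**The concern.** A paired t-test needs each observation in one sample to belong to a particular observation in the other. That link exists between baseline and month 3 in the same child. It does not exist between a child on curcumin and a child on placebo. The plan gives the paired t-test to the comparison without the link and the independent t-test to the comparison that has it.

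The treatment comparison is at stake. For any of IL-6, IL-10, hs-CRP or calprotectin judged to be normally distributed, the paired t-test is the only between-arm test that {20a} specifies. Followed as written, the result would rest on a pairing that someone has to invent.

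**Working it through.** **1. The sample size points to independent samples.** Sample size {14} treats the arms as two independent samples, with hs-CRP 5.9 (SD 2.57) and 3.6 (SD 1.58).

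- Pooled SD = sqrt((2.57² + 1.58²)/2) = 2.133.
- Standardised difference = 2.3/2.133 = 1.078.
- At two-sided 5% (assumed, as sidedness is not stated) and 80% power, the independent t-test needs 15 per arm, and 15/0.9 = 16.7, so 17 with 10% dropout.
- The stated 30 per arm would need a design effect of about 1.8 (15 × 1.8/0.9 = 30). The value used is not given, so the figure can be neither confirmed nor called wrong.

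What matters here is the basis: {14} uses independent samples, and {20a} contradicts it.

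**2. Each assignment against the design.**

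| Comparison | Data structure | Test if normal | Test if not normal |
|---|---|---|---|
| Between arms | independent | paired t: wrong | Wilcoxon rank-sum: valid |
| Within arm, before and after | paired | independent t: wrong | Mann-Whitney U: wrong |

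Wilcoxon rank-sum and Mann-Whitney U are the same two-sample test; on one simulated data set both gave p = 0.0459. Exchanging the words for between and within would correct both t-tests, but it would leave rank-sum on the paired comparison. No paired rank test is named.

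**3. Paired t-test on unpaired arms.** Two independent normal arms of 30 were simulated once (means 3.6 and 4.6, SDs 1.58 and 2.57; the 4.6 is an arbitrary choice for illustration). The independent t-test gave p = 0.047. Over 5,000 random pairings of the same data, the paired t-test gave p from 0.003 to 0.119, and 48% of the pairings fell at or below 0.05. The data were identical each time; only the row order changed.

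**4. Independent t-test on paired data.** With equal variance σ² at both visits and correlation ρ:

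- Correct SE of the mean change = sqrt(2σ²(1 − ρ)/n).
- SE used by the independent test = sqrt(2σ²/n).
- Ratio = 1/sqrt(1 − ρ).

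The documents give no ρ, so a range is assumed. The last column is the share of simulated trials of 30 children with no true change in which the independent t-test rejected at 5%.

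| ρ | SE ratio | Null rejection rate |
|---|---|---|
| 0 | 1.00 | 4.8% |
| 0.3 | 1/sqrt(0.7) = 1.20 | 2.2% |
| 0.5 | 1/sqrt(0.5) = 1.41 | 0.6% |
| 0.7 | 1/sqrt(0.3) = 1.83 | 0.1% |

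The error is on the conservative side: real changes within an arm would be missed.

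**The case against.** **It is a slip of wording.** This is probably true. The independent-samples basis in {14} and the comparison of changes in {12} show what was meant. But the text that governs the analysis says otherwise, and step 2 shows that exchanging the labels repairs only the t-tests.

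**The damage is limited.** Several parts of this stand:

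- For non-normal outcomes the between-arm test is correct as named. Which branch each marker will follow is unknown. Table 2 lists an IL-6 detection limit (2 pg/ml) above the upper end of its normal range (1.8 pg/ml), so a non-normal distribution is plausible there.
- With equal arm sizes, software would return a result. If the pairing were fixed without regard to the outcomes, the type I error for independent normal arms would stay nominal, and the cost would be mainly in degrees of freedom (29 instead of 58 at 30 per arm). The fault is that the result is arbitrary and cannot be reproduced without the row order.
- The ANCOVA is a valid between-arm analysis, but {20a} names it only for the secondary outcomes, and {20b} concerns additional analyses. Neither replaces the test stated for the primary outcomes.

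**Stronger readings that the documents do not support.** A reader might infer that efficacy will be judged from a significant change in one arm and not in the other, with a large false-positive risk. The article states no such rule, and {12} speaks of comparing changes. A reader might also infer that every primary test is invalid; the rank-sum branch shows that this goes too far. Nor is the absence of a statement on which comparison decides efficacy a fault here, since an analysis plan that is not shown may supply it.

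**Conclusion.** The point holds as an error in a stated rule, not as missing detail. Both t-tests in {20a} are on the wrong comparison, the within-arm Mann-Whitney U is wrong, and the between-arm rank-sum test is right.

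For normally distributed primary outcomes, the treatment comparison cannot validly be made as written. The p-value range in step 3 illustrates the arbitrariness in one simulated data set; it does not predict this trial's result. The inflation of the within-arm standard error by 1.20 to 1.83 rests on assumed correlations of 0.3 to 0.7 and equal variances at the two visits. It does not bear on the treatment comparison. The correction must be made because the error sits on the primary outcomes, although the intent is probably sound.

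**What to change.** Rewrite {20a} so that:

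- **Between arms**, change from baseline to 3 months is compared with the independent t-test or, if not normal, the Mann-Whitney U test. Alternatively, extend to the primary outcomes the ANCOVA with baseline and severity stratum already planned for the secondary ones.
- **Within arms**, change is assessed with the paired t-test or the Wilcoxon signed-rank test and reported descriptively.

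Rank-sum must be replaced by signed-rank for the within-arm comparison; exchanging the two labels is not enough. Any analysis plan should be checked for the same wording. The cost is a wording amendment. The sample size stays as it is, because {14} already assumes independent arms, and no data collection changes.

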#### Participant timeline {13}

Nutritional recommendations will be provided to all the patients and/or their parents and legal guardians stand on the CF requirements and adjustable CREON dosing to the level of dietary fat. In addition, the patients and their parents completed the CFQ depend on age.

Anthropometric measurements (weight and height) will be performed using a digital scale (model: SECA). Body weight will be measured without shoes, and height will be measured in the standing position without shoes with the heels stuck to the wall and the head looking frontwards with the accuracy of 0.5 cm.

The fecal examination will be performed before and after the intervention. Before intervention, fecal sample will be evaluated for bacterial over growth and parasite specially giardia by checking stool PH and trophozoites or cysts of giardia. Any positive result will be treated with antibiotics before stating the trials.

Blood sampling will be performed before and after the intervention. Approximately 5 mL of blood will be collected, immediately centrifuged, with the serum separated from the sediment, and preserved at the minimum of temperature of − 20 °C.

The primary and secondary consequences of the treatment will be investigated before and 3 months after the treatment. The clinical evaluation and follow-up of medication use and side effects will also be carried out via phone call and paying monthly visit to the clinic, and the findings will privately be presented to the patients (Table 2).

**Table 2 Tab2:** Laboratory measurements, equipment, and normal range

Test	Test equipment	Company	Quality control	Normal range
**Hs-CRP**	Biochemical auto analyzer	Pars azmoon	Intra-assay CV: 2.2% Inter-assay CV: 1.1% Linearity (*R*^2^): 0.99 Detection limit: 0.1 mg/lit	Children: up 2.8 mg/L Adult: up to 5 mg/L
**IL-6**	ELISA kit	Demeditec	Intra assay CV: 4.2% Inter assay CV: 4.9% Accuracy: 99% Specificity: 94% Detection limit: 2 pg/ml	Up to 1.8 pg/ml
**IL-10**	ELISA kit	pars gene (Invitrogen)	Intra assay CV < 3% Inter assay CV < 8% Detection limit:2 pg/ml	1.2–7.8 pg/ml
**Calprotectin**	ELISA kit	EUROIMMUN	Intra assay CV: 3.4% Inter assay CV: 6.4% Linearity(*R*^2^): 0.99 Sensitivity: 94.1% Specificity: 95.5% Detection limit:1.9 μg/g	50–120 μg/g: borderline > 120 μg/g: positive
**Nasopharyngeal swab**	URT-S&C (gram-positive, gram negative, pseudomonas)	Variable		Culture: negative WBC count: up to 2–3

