#### Sample size {14}

Due to the lack of clinical trials on the inflammatory effect of nano-curcumin in children with cystic fibrosis, we used HSCRP indices as an effect size. Therefore, the mean ± SD of hs-CRP indices in the curcumin and placebo groups were 5.9 ± 2.57 and 3.6 ± 1.58 respectively [27]. G- power analyzer was applied for calculating sample size between two independent populations with a confidence interval of 95% and power of 80%. By considering 10% dropout and using Deff (deign effect) for stratified sample, a total of 30 samples for each group was calculated. In total, 60 eligible patients with CF are needed to be included for the randomization aspect of this research.

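### Paired and unpaired tests are assigned to the wrong comparisons, and swapping the labels still leaves no paired rank test in the plan

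*Protocol article*

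**What the plan says.** Statistical methods {20a} assigns tests by type of comparison and by distribution.

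- Between groups: "intergroup differences will be evaluated using paired t-test for the normally distributed continuous variables and Wilcoxon rank-sum test for the other variables".
- Within groups: "Intragroup differences will be assessed using independent *t* test for the normally distributed continuous variables", and "Mann-Whitney *U* test for the other variables".

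Three other sections fix the structure of the data.

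- Trial design {8}: "This is a prospective, single center, double-blind, parallel, randomized placebo-controlled clinical trial".
- Participant timeline {13}: "The primary and secondary consequences of the treatment will be investigated before and 3 months after the treatment".
- Sample size {14} uses a calculation for "calculating sample size between two independent populations".

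Section {20a} also plans ANCOVA, adjusted for baseline and disease severity, for the secondary outcomes. Methods for additional analyses {20b} adds ANCOVA or logistic regression without naming outcomes.

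**The concern.** A paired test needs a natural link between two values. Here that link exists between a child's baseline and 3-month values. It does not exist between a child on curcumin and a child on placebo. The protocol attaches the paired t-test to the second comparison and the unpaired tests to the first.

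A reader may assume that the words for between and within were simply transposed. That does not repair the paragraph, because the rank test listed beside the paired t-test is the rank-sum test, and that test is unpaired.

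At stake is the stated analysis of the primary inflammatory markers, for which these sentences are the only tests clearly assigned. As written, the between-arm t-test has no defined pairing. On the charitable reading, every non-normal before/after comparison discards the pairing. Section {17a} says the data analysts are not blinded, so someone who knows the allocation would have to decide what was meant.

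**Working it through.** **Step 1: each test against the data it would be applied to.** The design, timeline and sample size sections make between-arm data unpaired and before/after data paired.

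| Comparison | Distribution | Literal reading | Fits? | Labels swapped | Fits? |
|---|---|---|---|---|---|
| Curcumin vs placebo | normal | paired t | no | independent t | yes |
| Curcumin vs placebo | non-normal | rank-sum | yes | Mann-Whitney U | yes |
| Before vs after | normal | independent t | no | paired t | yes |
| Before vs after | non-normal | Mann-Whitney U | no | rank-sum | no |

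The literal reading has three wrong cells of four, and the swapped reading has one. The before/after rank test is wrong on both.

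**Step 2: rank-sum and Mann-Whitney are one test.** On the same simulated two-sample data (30 + 30) both give P = 0.0584. The plan therefore names one unpaired rank test twice and no paired one.

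**Step 3: what an unpaired test does to before/after data.** Let ρ be the correlation between a child's two values and σ the common SD. The variance of the mean change is 2σ²(1 − ρ)/n, but an unpaired test uses 2σ²/n. Its statistic is too small by the factor √(1 − ρ), so in large samples the nominal 5% test has true level P(|Z| > 1.96/√(1 − ρ)).

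- ρ = 0.3: 1.96/√0.7 = 2.34, level 1.9%
- ρ = 0.5: 1.96/√0.5 = 2.77, level 0.6%
- ρ = 0.7: 1.96/√0.3 = 3.58, level below 0.1%

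Simulation with n = 30 (the planned arm size), bivariate normal values and a true change of 0.5 SD (40,000 runs per setting):

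| ρ (assumed) | Type I error, rank-sum | Type I error, signed-rank | Power, rank-sum | Power, signed-rank |
|---|---|---|---|---|
| 0 | 4.9% | 5.1% | 45% | 45% |
| 0.3 | 2.0% | 5.0% | 44% | 59% |
| 0.5 | 0.8% | 5.0% | 44% | 74% |
| 0.7 | 0.1% | 5.1% | 44% | 92% |

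The rank tests are meant for non-normal variables, so a second simulation used log-normal values (log-scale SD 0.8 and shift 0.4, which is 0.4/0.8 = 0.5 SD; 5,000 runs). Power was 44% for rank-sum against 68% for signed-rank at ρ = 0.5, and 44% against 87% at ρ = 0.7. Rank-sum type I error was 0.9% and 0.1%.

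**Step 4: what a paired t-test does between independent arms.** One dataset of 30 + 30 with a difference of 0.52 SD has independent-t P = 0.049. The paired t-test was applied to 20,000 random row orders of such a dataset. The central 95% of the P values ran from 0.018 to about 0.095, and about 44% of the orders gave P ≤ 0.05. The data are the same throughout; only the arbitrary matching of rows changes. If the arms differ in size, the test cannot use all children.

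The protocol attaches no figure to these test sentences, so there is none to reproduce. The 30 per arm from section {14} serves only as n.

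**The case against.** The strongest reply is that this is a slip of wording. The labels were transposed and signed-rank was written as rank-sum, and a competent statistician would not pair children across arms. On that reading both between-arm tests are right. The one wrong cell concerns within-arm change, which does not estimate the treatment effect, and with positively correlated values the error is conservative. It would not produce a false claim of efficacy.

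The consequences also have limits, and these stand:

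- On the literal reading the between-arm test for non-normal variables is valid, so the row-order problem concerns normally distributed variables only.
- The row-order example is one borderline dataset, not a long-run error rate. With equal arms and row order unrelated to outcome, the paired t-test keeps its level (about 5% in simulation, as for the independent test). It loses about one point of power: 79% against 80% at a standardised difference of 0.74.
- The rank-sum loss depends on the assumed correlation. At ρ = 0 there is none.
- ANCOVA is a valid between-arm method, but {20a} states it for secondary outcomes only. Section {20b} does not say that it covers the primary markers, and neither section supplies a paired rank test.

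The reply does not make the text correct. It needs two separate guesses about what was meant, and a plan fixed in advance should leave no such guess to an unblinded analyst.

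**Conclusion.** The concern holds. The paragraph is wrong on either reading, though not in every cell: three of four on the literal reading, one of four with the labels swapped. The Wilcoxon signed-rank test appears nowhere.

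The more serious consequence is on the literal reading: the between-arm t-test for normally distributed outcomes, including primary markers, rests on an arbitrary pairing. That is a fault of specification and reproducibility, not of inflated type I error when arms are equal. On the swapped reading the harm is confined to within-arm comparisons of non-normal variables. With 30 children, a change of 0.5 SD and a correlation of 0.5 to 0.7, rank-sum has about 44% power where signed-rank has 74% to 92% on normal data, or 68% to 87% on log-normal data. The correlations, shift and distributions are assumptions; the protocol gives none of them.

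This must be corrected before analysis, because the named tests do not fit the data of the primary outcomes.

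**What to change.** Rewrite the two sentences in {20a}:

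- Between groups (curcumin vs placebo): independent t-test or the adjusted model, with the Mann-Whitney U test as the rank alternative.
- Within groups (before vs after, descriptive): paired t-test, with the Wilcoxon signed-rank test as the rank alternative.

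Remove the rank-sum test as the partner of the paired t-test. The cost is two sentences of protocol wording, with no effect on data collection, patients or budget.

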#### Outcomes {12}

The primary outcomes of the current trial are the compared changes in the blood vessel inflammation, nasopharyngeal swab, and fecal samples at baseline with 3 months after the intervention: systemic inflammation by assessing IL-6 as an inflammatory agent, IL-10 as an anti-inflammatory agent, and hs-CRP level in the blood samples, pulmonary inflammation with the neutrophil count, bacterial/viral culture on the nasopharyngeal swab, and gastrointestinal inflammation with the calprotectin level in the fecal samples.

The secondary outcomes are changes in clinical assessment of the pulmonary symptoms via spirometry, anthropometric assessment stand on the BMI Z score, and evaluation of the quality of life using the CFQ from the baseline to 3 months of the intervention.

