### Data collection and management

#### Plans for assessment and collection of outcomes {18a}

As the primary outcome of the present study, blood vessel inflammation will be assessed in the sample using the ELISA assay (IL-6, IL-10, and hs-CRP), stool inflammation will be determined by measuring the calprotectin level using the ELISA assay, and pulmonary inflammation will be evaluated using the smear and culture (gram-positive, gram-negative, pseudomonas) of the nasopharyngeal soap. All the tests will be performed at the Buali Research Institute by expert personnel. Table 2 shows the performance specifications of the applied methods.

For the quality assurance of the employed laboratory methods, the performance specifications will be verified before using the kits for the analysis of the patient samples. All the tests will be performed in duplicate, and the standard curve will be prepared using the serial dilutions of the standard samples. The obtained results will be calculated from the standard curve after adjustment for the blank.

The secondary outcome of the present study was anthropometric assessment, which will be performed in a standard position using SECA instruments for height and weight. In addition, the WHO growth standard charts will be used for the evaluation of the BMI *z*-score.

In the current trial, we will apply the CFQ-R to assess the effects of nano-curcumin on the quality of life of the children with CF. The CFQ was first developed in France and consists of three appropriate versions for children aged 6–13 years (CFQ-child), as well as the parents of children with CF aged 6–13 years (CFQ-parent) and adolescents and adults with CF aged 14 years (CFQ-teen/adult) [28]. After the psychometric assessment of the original version and slight modifications, the final version of the CFQ-R was developed.

Spirometry will be performed using a spirometer (CHESTGRAPH HI-105), with the patients in a stable, standing position and their neck completely straight. To increase accuracy and reliability, the test will be repeated at least twice. If FVC and FEV1 are more than 150 ml different from the first time, the test will be repeated; the maximum repetition will be eight times.

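### Each secondary outcome has an unadjusted test and an ANCOVA, both significant at P ≤ 0.05, and the protocol does not say which decides.

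*Protocol article*

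**What the plan says.** All references are to the protocol article.

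- **Outcomes {12}** names three secondary domains: "changes in clinical assessment of the pulmonary symptoms via spirometry, anthropometric assessment stand on the BMI Z score, and evaluation of the quality of life".
- **Statistical methods {20a}** lists two sets of unadjusted tests. One sentence reads "intergroup differences will be evaluated using paired t-test for the normally distributed continuous variables and Wilcoxon rank-sum test for the other variables", the next "Intragroup differences will be assessed using independent *t* test for the normally distributed continuous variables and Mann-Whitney *U* test for the other variables". The labels are evidently swapped, since a paired t-test cannot compare two independent arms. For non-normal variables both sentences name the same two-sample test, because the Wilcoxon rank-sum test and the Mann-Whitney test are equivalent.
- **The same section** then says of the secondary outcomes: "The mean changes in the secondary outcomes will also be adjusted for the baseline data and disease severity using the analysis of covariance (ANCOVA".
- **It closes with one threshold for everything:** "In all the statistical analyses, the *P* value of ≤ 0.05 will be considered significant".
- **Additional analyses {20b}** says again that baseline and severity will be controlled, by ANCOVA or logistic regression. It does not rank that analysis against the unadjusted one.

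**The concern.** The section makes ANCOVA an addition to the unadjusted comparison, not a replacement, and gives both the same threshold. A borderline secondary outcome can pass one test and fail the other. The rule as written would then let whichever passed be called significant, so the error rate per outcome is no longer the stated 5%.

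Two features of the trial make this worth settling in advance. The secondary outcomes are its only clinical measures (lung function, growth and quality of life), and the abstract's aim covers clinical as well as inflammatory markers. Section {17a} also says the data analysts are not blinded, so the person holding both P values may know the allocation.

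**Working it through.** The article states no error rate for the secondary outcomes, so there is no figure of its own to reproduce.

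**Inputs from the article.** Threshold 0.05 ({20a}; sidedness is not given, two-sided assumed). 30 per group ({14}). Three secondary domains ({12}), each analysed as change from baseline.

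**Assumed inputs.** Correlation *r* between baseline and month 3: 0.5, 0.7, 0.9. Correlation between outcomes: 0, 0.3, 0.6. Normal data and no treatment effect.

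**Step 1: one outcome, both tests.** With equal variances σ² at both times, the change-score comparison has variance proportional to 2(1 − *r*)σ² and the ANCOVA to (1 − *r*²)σ². The variance ratio is (1 + *r*)/2, and the two test statistics have correlation √((1 + *r*)/2). The chance that at least one exceeds ±1.96 follows from the bivariate normal distribution:

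| *r* | correlation of the two tests | either test significant | same, favourable direction only |
|---|---|---|---|
| 0.5 | 0.866 | 7.3% | 3.7% |
| 0.7 | 0.922 | 6.8% | 3.4% |
| 0.9 | 0.975 | 6.0% | 3.0% |

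A null simulation (30 per arm; t-test on change plus ANCOVA with baseline and severity; 4,000 trials per setting) agrees. Averaged over nine settings at each *r*, it gives 7.3%, 6.8% and 6.3%. Single settings run from 5.5% to 7.8%, which is mostly simulation noise. A second simulation with 27 per arm gives 7.3%, 6.7% and 6.2%.

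**Step 2: three domains, one test each.** If independent, 1 − 0.95³ = 14.3%. At a between-outcome correlation of 0.5 the rate is 12.6%. The simulated settings lie between 11% and 15%. In the favourable direction, 1 − 0.975³ = 7.3% if independent.

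**Step 3: three domains, both tests.** If independent, 1 − (1 − 0.073)³ = 20% at *r* = 0.5. Simulated rates of at least one false-significant result, with the favourable-direction rate in brackets:

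| correlation between outcomes | *r* = 0.5 | *r* = 0.7 | *r* = 0.9 |
|---|---|---|---|
| 0 | 20.1% (10.8%) | 19.2% (9.8%) | 18.0% (8.9%) |
| 0.3 | 19.9% (9.4%) | 18.2% (9.1%) | 18.3% (8.5%) |
| 0.6 | 16.7% (8.5%) | 16.2% (7.9%) | 14.6% (7.5%) |

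**Step 4: how much the second test adds.** ANCOVA alone gives 14.1% in the top-left setting and 11.8% in the bottom-right. The differences are 20.1 − 14.1 = 6.0 and 14.6 − 11.8 = 2.8 percentage points. The duplicate test therefore adds about 3–6 points, and the rest comes from having three domains.

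**Step 5: if more measures are tested.** Section {18a} mentions FEV1 and FVC in its spirometry repeatability rule. It also describes a CFQ version for children aged 6–13, "as well as the parents of children with CF aged 6–13 years (CFQ-parent". With four measures and both tests, the simulated rate is 17.8–27.0% in either direction and 8.8–15.0% in the favourable direction.

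**Not counted.** The within-group tests, and the choice between t-test and rank test after a normality check. In the simulation, severity is a covariate unrelated to outcome, and the stratified allocation is not modelled.

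**The case against.** **The duplicate test is a small problem.** This stands. It moves one outcome from 5% to about 6–8%, and reporting adjusted and unadjusted results together is common. What the article lacks is a statement of which one carries the conclusion.

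**Section {20b} already ranks them.** It places baseline and severity adjustment under additional analyses, so ANCOVA might be read as a supplement to the unadjusted test. That is a possible reading, but {20b} does not say so, and {20a} puts both under its methods for primary and secondary outcomes with one threshold.

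**The unadjusted between-arm test is an interpretation.** For normally distributed variables this is true, because the labels must be read as swapped. For other variables it hardly matters, since both sentences name a two-sample rank test.

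**A reader might infer more than the article supports:**

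- *That a false claim of clinical benefit has roughly a 20% chance.* Figures of that size count significant results in either direction, including apparent harm. In the favourable direction, three domains give about 8–11%. No section says that a conclusion of benefit will rest on one significant secondary outcome.
- *That four or more measures will be tested.* FEV1 and FVC appear together only in a test-quality rule, and the article does not say that child and parent CFQ scores will be tested separately.
- *That the lack of a testing order, alpha split or exploratory label is itself an error.* A condensed article commonly leaves these to an analysis plan, which is not at hand. The point rests on what {20a} does fix: two analyses, one threshold and no deciding test.

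**Conclusion.** The point holds in a limited form. Section {20a} gives each secondary outcome two between-arm analyses, both significant at P ≤ 0.05, and names neither as decisive. If either may count, the two-sided false-positive rate is about 6–8% per outcome. Over three domains it is about 15–20% for any false-significant result and about 8–11% in the favourable direction. With one test per domain the any-direction rate is about 13–14%. These figures assume a baseline-to-follow-up correlation of 0.5 to 0.9 and a between-outcome correlation of 0 to 0.6. They would be higher if more measures were tested. The matter concerns secondary outcomes only. It is worth correcting because the correction costs almost nothing.

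**What to change.** In {20a}, state that the ANCOVA adjusted for baseline and disease severity is the single deciding between-arm test for each secondary outcome, and that any unadjusted comparison is descriptive only. Add that secondary results are presented as supportive estimates with 95% confidence intervals. Correct the intergroup and intragroup labels in the same edit, so that the descriptive comparison is identifiable.

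ANCOVA is the natural choice. It adjusts for the severity factor that stratifies the randomisation, and its variance is (1 + *r*)/2 of the change-score variance: 75%, 85% or 95% at *r* = 0.5, 0.7 or 0.9. One deciding test restores 5% per outcome. Three independent domains would still give 14.3% for any false-significant result, which is why the results should be described as supportive.

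The cost is one or two sentences, with no new data or patients. The small downside is that an isolated P ≤ 0.05 from the unadjusted test can no longer be claimed as a significant effect.
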